### Sample size

2.2

The sample size calculation is based on the 2017 randomized controlled trial report of Ning et al^[8]^ who used acupoint catgut embedding to treat prediabetic patients. In this study, the reversal rate of impaired glucose regulation to Normal Glucose Tolerance is estimated as the outcome. We assume that after 3 months of treatment, the reversal rate of the treatment group is 57% and the reversal rate of the control group is 20%. The test levels (α = 0.05 and β = 0.2) are set. The PASS 2008 software (Beijing HuanZhongRuiChi Technology Co., Ltd.) calculates that the sample size of each group is 25, and 50 in the 2 groups. Assuming 15% drop out, a total of 60 participants will be needed to achieve statistical significance, so each group is required to have 30 participants.

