### Randomization procedure and concealment of allocation

2.6

Clinicians will recruit volunteers who meet the research criteria. Patients entering the trial will be randomly assigned to a treatment group or a control group. Randomization will be programmed with SAS 9.2 in the clinical Research and data Center of Guangzhou University of Chinese Medicine. A computer-generated block assigned participants to a treatment or control group on a 1:1 scale. A staff member, independent of this study, will complete the random assignment. The random list will be kept strictly confidential until the study began.

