## Statistical analysis

5

In this study, the conversion rate from IGT to normal blood glucose between baseline and follow-up period was the main outcome indicator. Statistical analysts will use a one-sided *t* test to compare between the 2 groups. The 2 groups will be compared using the 95% confidence interval method to determine the advantage. Data will be statistically analyzed using PASW Statistics 18.0 (IBM SPSS Inc., Armonk, NY) and SAS 9.2 software (SAS Institute Inc., Cary, NC). For secondary results, a 2-tailed *P* value *<* .5 will be considered statistically significant. For safety evaluation and analysis, first use descriptive analysis, and then use tests to compare the incidence of adverse reactions between the 2 groups. When comparing, consider the severity of adverse reactions and the degree of causation with the intervention. The categorical variables between the 2 groups were compared using Fisher exact test and chi-square test.

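### The primary comparison is given both a one-sided test and a 95% confidence interval, with no level, no interval sidedness and no deciding rule, so the two can give opposite answers

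*Protocol article*

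**What the plan says.** Section 5 (Statistical analysis) names the conversion rate as the main outcome and continues: "Statistical analysts will use a one-sided *t* test to compare between the 2 groups". The next sentence reads: "The 2 groups will be compared using the 95% confidence interval method to determine the advantage". Both sentences concern the same comparison. Two-tailed testing is mentioned only for the secondary results.

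The only design error rate is in section 2.2 (Sample size): "The test levels (α = 0.05 and β = 0.2) are set". That section assumes that "the reversal rate of the treatment group is 57% and the reversal rate of the control group is 20" per cent, and reports that the software "calculates that the sample size of each group is 25, and 50 in the 2 groups". It then allows for dropout: "Assuming 15% drop out, a total of 60 participants will be needed to achieve statistical significance". It names neither the test procedure nor the sidedness behind the 25.

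**The concern.** A one-sided test at 0.05 pairs with a 90% two-sided interval. A 95% two-sided interval pairs with a two-sided test at 0.05, which is one-sided 0.025 in the direction of interest. Naming the first test and the second interval for one comparison, without ranking them, gives the trial two thresholds for success.

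A result that falls between the thresholds could be reported as positive by the test or as inconclusive by the interval. The choice could be made after the data are seen. The sample size section does not settle it, because its α has no stated sidedness.

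**Working it through.** **Inputs.** Rates 57% and 20%, α = 0.05, power 80%, 25 per arm, 15% dropout and 30 per arm enrolled (section 2.2); 1:1 allocation (section 2.6); one-sided test and 95% interval (section 5).

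**1. The plan's own figure.** Pooled formula for two proportions, with mean rate p̄ = (0.57 + 0.20)/2 = 0.385:

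n = [z_α √(2p̄(1−p̄)) + z_β √(p₁(1−p₁) + p₂(1−p₂))]² / (p₁−p₂)²

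- The two roots are √0.47355 = 0.6881 and √0.4051 = 0.6365; z_β = 0.8416.
- Two-sided 0.05 (z = 1.960): n = 25.94, so 26.
- One-sided 0.05 (z = 1.645): n = 20.31, so 21.

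The table shows exact power, from enumerating all binomial outcomes at 57% against 20%:

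| n per arm | chi-square, two-sided 0.05 | chi-square, one-sided 0.05 | Fisher, one-sided 0.05 |
|---|---|---|---|
| 20 | 69.2% | 78.9% | 69.2% |
| 21 | 71.9% | 81.0% | 69.4% |
| 24 | 78.5% | 86.3% | 78.5% |
| 25 | 81.1% | 88.1% | 81.1% |
| 30 | 85.6% | 91.3% | 86.4% |

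The one-sided t test gives the same power as the one-sided chi-square test at these sizes. So 25 is the first size to reach 80% for a two-sided chi-square test, while the one-sided t or chi-square test gets there at 21. One-sided Fisher also first reaches 80% at 25, and the one-sided continuity-corrected formula gives 26. The dropout step reproduces: 25/0.85 = 29.4, so 30 per arm and 60 in total.

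**2. Can the two rules disagree?** Take the test at one-sided 0.05 and a two-sided Wald 95% interval for the risk difference, with 12/30 against 6/30:

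- Difference = 0.40 − 0.20 = 0.20.
- t test: pooled SE = 0.1174, t = 0.20/0.1174 = 1.703 on 58 df, one-sided P = .047. Positive.
- Interval: SE = √(0.40×0.60/30 + 0.20×0.80/30) = 0.1155; 0.20 ± 1.96 × 0.1155 = −0.026 to +0.426. Not positive.

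At 25 per arm, 11/25 against 5/25 gives P = .036 and an interval of −0.010 to +0.490, the same conflict.

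**3. How often?** With 30 per arm, the trial is positive by the test and null by the Wald interval in 10.1% of trials if the true rates are 40% and 20%, and in 4.8% at the protocol's own 57% and 20%.

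**4. Error in favour of acupuncture.** True rate 20% in both arms, exact:

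| Rule | 25 per arm | 30 per arm |
|---|---|---|
| t test, one-sided 0.05 | 5.2% | 5.4% |
| t test, two-sided 0.05 (acupuncture direction) | 2.7% | 2.5% (0.0245) |
| Wald two-sided 95% interval above 0 | 3.0% | 3.0% |

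At 30 per arm the ratio is 0.0545/0.0245 = 2.2 against the two-sided test and 0.0545/0.0302 = 1.8 against the Wald interval.

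**5. Readings under which the conflict goes away.** If the one-sided test is run at 0.025, or the 95% interval is a one-sided bound, the two rules share the same nominal error and agree, apart from small differences in how the standard error is computed.

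**The case against.** The strongest reply is that the article never sets one-sided 0.05 for the primary test and never calls the interval two-sided. Reading the interval sentence as directional is possible, since it speaks of determining the advantage, and a one-sided 95% bound would agree with a one-sided 0.05 test. A one-sided superiority test is also legitimate when its level is stated. All of this stands. A reader might infer that the plan definitely doubles the error in favour of acupuncture; the text supports that only under the two assumptions in step 2.

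A reader might also infer that 25 per arm proves a two-sided design. It does not: one-sided Fisher gives exactly 25, and section 5 names Fisher alongside chi-square for categorical variables.

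The sizes depend on method. With one-sided Fisher the error at 30 per arm is 2.3%, and 12/30 against 6/30 gives P = .079, so that example no longer conflicts. But section 5 names a t test for the main outcome, and the figures above use that test.

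It is tempting to add that the trial is unblinded. Patients and treating clinicians are, but the outcome assessor is blinded (sections 2.8 and 4) and the endpoint is laboratory glucose. The point does not rest on blinding.

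Finally, an unseen full protocol or analysis plan might settle the level and the deciding rule. That would excuse silence. Here, however, the article states two rules that, on their usual reading, do not match.

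**Conclusion.** The point holds in conditional form. Two decision rules are stated for one primary comparison, and the article gives no level for the test, no sidedness for the interval and no precedence. With the only stated α used one-sided and a conventional two-sided 95% interval, they conflict for one-sided P between about .025 and .05, and the false-positive chance in favour of acupuncture is about 5.4% rather than 2.5% to 3.0% (30 per arm, 20% in both arms). The stated sample size is consistent with two-sided 0.05 and does not match the one-sided t test named in section 5, but it cannot by itself show which was intended. The enrolled 60 is adequate under either rule.

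**What to change.** State one sidedness, one α and one deciding rule, in the same terms in sections 2.2 and 5. The preferred version is two-sided α = 0.05, with superiority concluded if the two-sided 95% confidence interval for the risk difference excludes 0 in favour of acupuncture, and with the words calling the test one-sided removed. Keeping a one-sided test at 0.025 with that same interval is an equivalent repair. In either case, take the P value and the interval from matching methods so that they cannot disagree, and name in section 2.2 the procedure and sidedness that gave 25.

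This is a wording change and adds no participants. Compared with one-sided 0.05, exact power at 25 per arm is 81% rather than 88% (78.5% rather than 87.0% by the pooled formula). At the enrolled 30 per arm it is about 86%, above the 80% target.

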**Methods and analysis::**

This study is a prospective randomized controlled trial in which 60 patients with prediabetes will be randomly allocated in a 1:1 ratio into either an acupuncture treatment group or a control group. Prediabetes patients in the control group will receive prediabetes health education for lifestyle interventions, whereas patients in the acupuncture group will receive lifestyle interventions plus Zuo Daliji and Yueku stitch treatment. Twenty-four treatment sessions will be performed over 3 months. The primary outcome is conversion rate from prediabetes to normal blood glucose. Secondary outcomes include fasting plasma glucose, 2-hour plasma glucose, glycosylated hemoglobin and blood lipid concentration.

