### Secondary outcomes

2.10

Secondary outcomes include the following: FPG, 2-hPG after a 75-g OGTT, glycosylated hemoglobin and blood lipid concentration.

FBG and 2h-hPG will be tested at visit 1 (3 days before study), visit 4 (week 12) and the end of follow-up period. Other secondary outcomes will be tested only at visit 1 and visit 4 (Table 1).

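### The significance threshold for all secondary outcomes is printed as P < .5, so a comparison with no true effect has a 50% chance of being called significant.

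*Protocol article*

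**What the plan says.** Section 5 (Statistical analysis) gives a complete decision rule for the secondary outcomes, with scope, sidedness and cut-off: "For secondary results, a 2-tailed *P* value *<* .5 will be considered statistically significant".

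Section 2.10 defines what the rule covers: "Secondary outcomes include the following: FPG, 2-hPG after a 75-g OGTT, glycosylated hemoglobin and blood lipid concentration". On timing it adds: "FBG and 2h-hPG will be tested at visit 1 (3 days before study), visit 4 (week 12) and the end of follow-up period". The other secondary outcomes are measured only at visits 1 and 4.

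Two other places give an error rate or confidence level. Section 2.2 (Sample size) says "The test levels (α = 0.05 and β = 0.2) are set", for the reversal rate. Section 5 plans a 95% confidence interval for comparing the two groups. Neither states a threshold for the secondary outcomes.

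**The concern.** A two-tailed P value below .5 is hardly a criterion at all. When there is no effect, a valid test gives P below .5 half the time. The rule covers secondary results without exception, so it reaches fasting and 2-hour glucose, the two measurements that define the primary outcome (section 2.9), as well as glycosylated hemoglobin and lipids.

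What is at stake is the label. Under the printed rule, a P value of .4 for glycosylated hemoglobin or lipids could be reported as significant by a criterion fixed in advance. That label would then say almost nothing about whether acupuncture adds to lifestyle intervention. A threshold is fixed in advance so that it need not be settled after the results are seen, and a threshold nobody would defend leaves that question open.

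**Working it through.** **Inputs**
- Secondary threshold: two-tailed P < .5 (section 5).
- Reference level: α = 0.05 (section 2.2), consistent with the 95% interval (section 5).
- Group size: 30 per arm, 60 in total (section 2.2).
- Outcomes and times: fasting and 2-hour glucose at week 12 and at the end of follow-up (week 24, section 2.8); glycosylated hemoglobin and lipids at week 12 (section 2.10).
- Number of lipid fractions: not stated. I take 1 or 4, as an assumption.

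**1. The plan's own calculation.** With 57% against 20%, two-sided α = 0.05 and power 0.80, the usual formulas for two proportions give 24 per group (unpooled variance) or 26 (pooled, no continuity correction). The stated 25 lies between them. Inflating for dropout gives 25 / (1 − 0.15) = 29.4, hence 30 per group. The sample size is therefore consistent with α = 0.05 and owes nothing to the .5 in section 5.

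**2. Error rate per comparison.** The type I error of a valid two-sided test equals its threshold: 0.50 as printed, against 0.05. The ratio is 0.50 / 0.05 = 10. A simulation of 100,000 two-sample t tests with 30 per arm and no true difference rejected 50.1% of the time at .5 and 5.1% at .05.

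**3. How small a difference would pass.** With 30 per arm there are 58 degrees of freedom. The critical |t| is 0.68 at .5 and 2.00 at .05. The smallest observed difference called significant, in standard deviations, is t × √(2/30):
- at .5: 0.679 × 0.258 = 0.18 SD
- at .05: 2.002 × 0.258 = 0.52 SD

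**4. Number of comparisons.** Two glucose measures at two post-baseline times, plus glycosylated hemoglobin, plus lipids counted once: 2 × 2 + 1 + 1 = 6. With four lipid fractions: 2 × 2 + 1 + 4 = 9.

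**5. False positives over the set, no true effect.** The expected number is k × threshold. The chance of at least one is 1 − (1 − threshold)^k if the comparisons are independent.

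| Comparisons | Expected at .5 | At least one at .5 | Expected at .05 | At least one at .05 |
|---|---|---|---|---|
| 6 | 3.0 | 1 − 0.5^6 = 98.4% | 0.30 | 1 − 0.95^6 = 26.5% |
| 9 | 4.5 | 1 − 0.5^9 = 99.8% | 0.45 | 1 − 0.95^9 = 37.0% |

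**6. Sensitivity.** If outcomes are counted without separate visits, there are 4 comparisons, or 7 with four lipid fractions. The chance of at least one at .5 is then 93.8% or 99.2%. For correlated outcomes, a simulation with a common correlation of 0.7 (illustrative) and 6 to 9 comparisons gives about 93% to 97% at .5 and about 16% to 20% at .05. The expected counts in step 5 and the 50% per comparison do not depend on independence.

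**7. Conflict inside section 5.** A secondary comparison with P = .3 is significant under the printed rule, yet its 95% interval includes no difference. Every P value from .05 up to .5 produces this contradiction.

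**The case against.** The strongest reply is that this is a dropped zero, not a choice. The other error-rate figures in the article are conventional, and an analyst would very likely use .05 regardless. I agree that a misprint is the likely explanation. It does not settle the matter: the α in section 2.2 belongs to the sample size for the primary outcome, and no sentence can be cited that replaces .5 for the secondary outcomes.

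The second reply is that the threshold changes only the word significant. The data, the estimates and the P values are the same, and a reader shown P = .3 can judge it. This is right, and it limits the harm: the secondary estimates keep their value, while claims of significance lose theirs.

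The third is that the familywise figures rest on a constructed count and on independence, although these outcomes come from the same patients and are clearly correlated. That also stands, so those figures are illustrative. The contrast survives a correlation of 0.7, and the main result needs neither assumption.

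Finally, the error is confined to secondary outcomes. The primary outcome, the sample size and the conduct of the trial are untouched.

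**Conclusion.** The point holds and must be fixed. The printed rule gives each secondary comparison a 50% type I error, ten times the α used to size the trial, and it contradicts the 95% interval in the same section. This rests only on the printed threshold and on the tests being valid. The figures over the whole set (3.0 to 4.5 expected false positives, 98% to 99.8% chance of at least one) also rest on 6 to 9 comparisons and, for the percentages, on independence. The likely cause is a misprint, but the sentence is a decision rule that is wrong as it stands.

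**What to change.** In section 5, change the threshold for secondary results from .5 to .05, keeping it two-tailed. If the analysis plan, which is not shown, repeats the figure, correct it there too. Make and date the correction before the secondary outcomes are analysed, so that it cannot look as though it was chosen with the results in hand.

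Even at .05 the chance of at least one false positive over 6 to 9 independent comparisons is 26% to 37%. It is therefore sensible to report each secondary outcome as an effect estimate with a 95% confidence interval and to describe these outcomes as supportive of the primary one. This is advice on reporting and not part of the correction; it extends the interval approach section 5 already takes.

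The cost is one number in the text. Visits, measurements and sample size do not change. Fewer secondary results will be called significant.

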[name] comprehended the principles of Dong extra acupoints, combined with Taoism, and established a simple and delicate acupuncture system based on traditional acupuncture. Zuo acupuncture has the advantages of less acupuncture points, simple operation, and no need for acupuncture sensation, which may reduce patients’ pain and fear. Zuo acupuncture has achieved good effect in regulating blood glucose and treating diabetic complications by controlling blood glucose. Zuo Daliji and Yueku stitch are a type of Zuo acupuncture. In a randomized controlled trial, Zhu Jingzhi was given hypoglycemic drugs and methylcobalamin and prostaglandin E1 in the control group (n = 30), and the treatment group (n = 30) combined with Daliji stitch and microcollaterals thorning blood therapy on the basis of oral drugs. The results show that the Daliji stitch combined with micro-collateral puncture can significantly relieve and improve the clinical symptoms of patients with diabetic peripheral neuropathy.^[11]^ Li Yang divided 60 patients with prediabetes into a control group (n = 30) and an acupuncture group (n = 30). The control group was given relevant education to improve lifestyle. The acupuncture group was treated with Zuo Liji stitch based on lifestyle intervention. The result shows that acupuncture Liji stitch can more effectively reverse the prediabetes to normal blood glucose.^[12]^ On the basis of point selection of LiJi stitch, Zusanli (ST36), dacha and Taichong (LR3) are added, which is Zuo Da Li Ji and Yue Ku stitch. This treatment is effective in controlling blood glucose and help restore normal blood glucose levels in patients with prediabetes. However, the exclusive effectiveness of Zuo Daliji and Yueku stitch in individuals with prediabetes is not well documented. The objective of this trial is to clarify the clinical effectiveness and safety of Zuo Daliji and Yueku stitch for prediabetes.

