### Intervention

2.7

A total of 60 patients with prediabetes will be recruited. The patients will be randomly assigned to 2 different groups: the treatment group and the control group. Participants in the control group will receive prediabetes health education for lifestyle interventions for 12 weeks, whereas participants in the acupuncture group will receive lifestyle interventions plus Zuo Daliji and Yueku stitch treatment twice a week for 12 weeks. All of the researchers in the study will receive professional training on prediabetes before participating. All acupuncturists will receive the same training under the clinical treatment plan before the study to standardize the procedures performed by the different acupuncturists. During the trial, in addition to the research interventions, other treatments for blood glucose control will be prohibited.

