## Safety

3

We will conduct electrocardiogram, liver function, and renal function tests on all participants during the screening phase to exclude patients with severe organic damage. For recording the test period appeared adverse reactions, such as treatment in syncope, local irritation, infection, hemorrhage, stabbing pain unbearable, hysteresis, curved needle, needle acupuncture treatment for sustained severe local pain after 1 hours. Researchers should be on the watch list in cases recorded the degree of symptoms or disease, date of onset, frequency, duration, mitigation, treatment measures and treatment after date, results and follow-up. When an adverse event is found, the observing physician may decide whether to suspend the observation according to the condition. If serious adverse events occur, the unit undertaking the clinical trial shall immediately take necessary treatment measures to protect the safety of the subjects. All adverse events should be followed up and recorded in detail until they are properly resolved or stable.

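### The planned between-arm test of adverse reactions does not set apart needle-specific reactions, which cannot occur in a control arm that receives no needles

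*Protocol article*

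**What the plan says.** The Introduction makes safety part of the aim: "The objective of this trial is to clarify the clinical effectiveness and safety of Zuo Daliji and Yueku stitch for prediabetes".

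The Safety section gives an open list of reactions to record. It begins "such as treatment in syncope, local irritation, infection, hemorrhage, stabbing pain unbearable" and continues "hysteresis, curved needle, needle acupuncture treatment for sustained severe local pain after 1 hours". I read hysteresis and curved needle as stuck and bent needle. The same section also asks that all adverse events be followed and documented.

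On the comparator, the Intervention section states: "Participants in the control group will receive prediabetes health education for lifestyle interventions for 12 weeks". There is no sham procedure.

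The Statistical analysis section sets the safety analysis: a descriptive step comes first, and the analysts then "use tests to compare the incidence of adverse reactions between the 2 groups". It adds that severity and the causal link to the intervention are to be considered, and ends: "The categorical variables between the 2 groups were compared using Fisher exact test and chi-square test". It states no significance level for safety.

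**The concern.** The reactions named for recording mix two kinds of event. Stuck needle, bent needle and lasting pain after needling need a needle. Syncope, infection, bleeding and irritation are typical of needling but could arise in anyone. The plan applies one between-arm test to adverse reactions without distinguishing the two kinds.

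For the needle-specific items the comparison is settled by design. Controls cannot have them, so a single such reaction in the acupuncture arm already shows that the rates differ. Whether P falls below a threshold then depends on the sample size and on the test chosen, and says little about how often patients are harmed. The useful quantity is the frequency in the acupuncture arm, with its precision. Safety is part of the stated objective, so the analysis should deliver that quantity.

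**Working it through.** **Inputs.** Sample size: 30 per group, and 25 per group before the 15% dropout allowance. Treatment course: 24 sessions per participant, so up to 24 × 30 = 720 sessions in the acupuncture arm. Intervention: no needles in the control arm, so 0/30 for needle-specific items. Statistical analysis: Fisher and chi-square both named. Assumption: two-sided 0.05, because no level is given for safety.

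**The plan's own figure.** No figure is given for the safety comparison. The only sample-size figure is for efficacy (57% against 20%, α = 0.05, β = 0.2): 25 per group. The two-sided normal approximation gives 26 with pooled variance and 24 with unpooled variance, so 25 is reproduced. Dropout: 25 / 0.85 = 29.4, rounded up to 30. The trial is sized for efficacy and this point leaves that untouched.

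**Tests of k/30 against 0/30.**
- Fisher, two-sided, equal arms: P = 2 × C(30,k) / C(60,k). For k = 5: 2 × 142,506 / 5,461,512 = 0.052.
- Chi-square, uncorrected: χ² = 60k / (60 − k). For k = 4: 240 / 56 = 4.29, P = 0.038.
- Chi-square with continuity correction: χ² = 60 × (30k − 30)² / [900 × k × (60 − k)]. For k = 5: 864,000 / 247,500 = 3.49, P = 0.062.
- Exact 95% interval for the acupuncture arm: Clopper-Pearson. For 0/30 the upper limit is 1 − 0.025^(1/30) = 11.6%.

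| Acupuncture arm | Fisher P | Chi-square P, uncorrected | Chi-square P, corrected | Exact 95% interval |
|---|---|---|---|---|
| 0/30 (0%) | 1 | not defined | not defined | 0% to 11.6% |
| 3/30 (10.0%) | 0.237 | 0.076 | 0.236 | 2.1% to 26.5% |
| 4/30 (13.3%) | 0.112 | 0.038 | 0.121 | 3.8% to 30.7% |
| 5/30 (16.7%) | 0.052 | 0.020 | 0.062 | 5.6% to 34.7% |
| 6/30 (20.0%) | 0.024 | 0.010 | 0.031 | 7.7% to 38.6% |

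Fisher is first significant at 6/30 and uncorrected chi-square at 4/30. At 4/30 and 5/30 the result therefore depends on which named test is run. With 25 evaluable per arm, Fisher for 5/25 (20%) against 0/25 gives P = 0.0502.

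**Chance of a non-significant result, 30 per arm, control count zero.** This is the binomial probability of at most 5 participants with a reaction (Fisher) or at most 3 (uncorrected chi-square).

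| True rate in acupuncture arm | Fisher | Chi-square, uncorrected |
|---|---|---|
| 10% | 93% | 65% |
| 15% | 71% | 32% |
| 20% | 43% | 12% |

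The document does not say what rate would be clinically important, so a range is shown.

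**The case against.** The best defence is that the plan does more than test. Description comes first, so 5/30 would be visible whatever the P value, and severity and causation are to be weighed. This stands. A reader might infer that the safety conclusion would rest on the P value alone, or that non-significance would be taken as evidence of safety. Neither is written anywhere in the document.

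A reader might also infer that every listed reaction has a control count of zero, or that the null hypothesis is meaningless throughout. That goes too far. The list is open, all adverse events are to be recorded, and infection, bleeding or syncope can occur in a control participant. Nor does the document suggest that controls would not be observed: Outcome measures schedules weeks 4, 8, 12 and 24 without restricting them to one arm. For general adverse events in an add-on trial, equal incidence is a proper null and the difference estimates the excess risk. The objection to testing holds only for the needle-specific items.

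It can also be said that Fisher is the conventional choice at such small expected counts (2.5 per arm with 5 events), that low power for harms is common to any trial of 60, and that exact intervals are details for an analysis plan. The first two points are fair; the 11.6% upper limit for 0/30 comes from the sample size, and the fix does not change it. The third does not remove the point, because the between-arm test is something the article states, and it is the stated choice that is questioned.

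**Conclusion.** The point holds in a limited form. The plan tests adverse reactions between arms without separating needle-specific reactions, and for those the control count is zero by design, so the test does not inform on safety. An observed 16.7% (5/30) would be non-significant by Fisher (P = 0.052) while compatible with a true rate anywhere from 5.6% to 34.7%; by uncorrected chi-square, 13.3% (4/30) would already be significant.

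This rests on an assumed two-sided 0.05 level and on 30 participants analysed per arm. The threshold of .5 printed for secondary results is a separate matter and is not used here. The claim does not extend to general adverse events, and the document does not commit the investigators to reading non-significance as safety. The primary outcome, sample size and efficacy inference are untouched. This is a minor point, worth correcting because the correction is cheap and safety belongs to the objective.

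**What to change.** In the Statistical analysis section, replace the single between-arm test with three statements.

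1. Needle-specific reactions (stuck or bent needle, lasting pain after needling) are reported in the acupuncture arm only, by severity, as participants affected and as events per session, with exact 95% confidence intervals. Intervals for the per-session rate allow for repeated sessions within a participant, since up to 720 sessions come from only 30 people.
2. The between-arm comparison is limited to all-cause adverse events, asked for in the same way in both arms at the existing visits (weeks 4, 8, 12 and 24), and given as a risk difference with a 95% confidence interval.
3. No safety conclusion is drawn from a non-significant P value.

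The cost is a change of wording and the same adverse-event question in both arms at visits already planned; no extra participants or visits are needed. The downside is that no P value is quoted for needling reactions.
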